**Figure 2 F2:**
[figure not shown]
Mediators and moderators to be assessed in exploratory analyses.

The clinicians will be included as a random effect, and intervention group, time, and baseline 5A scores will be included as fixed effects. The interaction between treatment and time will be used to assess whether the treatment effect (of the intervention) changes with time.

Secondary analyses include similar modeling approaches for the secondary outcome variables: autonomy support (mHCCQ), patient perceived competence (PCS) and clinician feasibility (PAL). Clinician feasibility will also be qualitatively analyzed using the process evaluation data and individual clinician exit interviews. The secondary hypotheses (H2-H4) are as follows:

H 2: The intervention will increase clinician use of the PCC construct autonomy supportiveness as assessed by the mHCCQ in the post-intervention period (immediately post and at one year) compared to baseline.

H 3: The intervention will increase patient perceived competence (accessed via the PCS) for adopting physical activity.

H 4: Specific patient recall of the Assist and Arrange will be associated with the greatest patient perceived competence to adopt physical activity compared to recall of Ask, Advise, or Assess.

Hypotheses 2–4 will be tested by measuring the changes in the mHCCQ, PCS, and PAEI scores, respectively, for patients seen by clinicians in Group 1 in the post-intervention period (immediately post and at one year) compared to baseline. compared to the Group 2 baseline and Group 1 baseline. We will also compare change in the 5A scores for Group 2 post-intervention compared to Groups 1 and 2 baseline scores.

Exploratory analyses will use a similar approach to that used for the primary analysis, to examine whether the primary outcome (5A score) was mediated by patient perceived competence (PCS score), clinician autonomy supportiveness (mHCCQ score), or patient recall of the 5As (PAEI score). Additional exploratory analyses will examine the role of selected factors that may moderate the relationship between the intervention and the 5A score: continuity of care, patient socio-demographic variables, patient BMI, baseline health, health behaviors, health literacy, and competing demands. Regression-based statistical models will be constructed and examined. The Diagram below shows the inter-relationship of the mediating and moderating factors to be explored in this analysis.

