### Data management

All questionnaires and measurements will be collected and entered into a secure protected database by the Research Assistants. Data will be entered on scannable forms and electronically sent to an Access database. After scanning, data will be audited visually for errors. SAS statistical packages are used for the analyses. Unless otherwise stated, all statistical tests will be performed at the two-tailed 5% level of significance. Likewise, 95% confidence intervals will be constructed for estimation of effects (e.g., difference in mean 5A scores across time points).

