### Statistical analyses

The primary outcome measure will be the 5A score as described in (section Primary outcome measure: 5As score). The primary analysis will use a mixed effect model to compare mean 5As scores between and within each group for each of the three time points: baseline, immediately post-intervention, and follow-up. The primary hypothesis (H1) is: Clinicians who complete the communication intervention will increase their use of all 5As for all visits in which the topic of physical activity is raised as judged by audio-recordings of office visits in the post-intervention period (immediately post and at one year) compared to baseline. Figure 2 shows the analysis plan for hypothesis testing and exploratory outcomes.

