### Sample size and power

The primary goal of this study is to evaluate the influence of a clinician communication intervention on use of the 5As in communication about physical activity in the post-intervention period (immediately post and at one year) compared to baseline as assessed by audio-recorded data. The sample includes a planned maximum of 15 clinicians (eight in Group 1 and seven in Group 2) measured at three (Group 1) or four (Group 2) time points. The measurements consist of a total of 25 audio-recorded patient visits from each clinician distributed across each of the evaluation points: approximately 10 recordings at baseline and seven or eight each at post- and follow-up points. Of the planned 375 recorded visits, we estimate up to 20% may be excluded from the analysis due to the patient or clinician shutting off the recorder, or equipment malfunction, thus leaving approximately 300 recorded visits (about seven per clinician per time point, or 20 total per clinician) for analysis. Pilot data with 46 recorded visits from eleven physicians showed that the average 5A score was 0.74, with a standard deviation of 1.06. Thus, with 15 clinicians and 20 patients per clinician, we will have 80% power to detect a difference of 0.54 between Groups 1 and 2, using a two-sided t-test at 0.05 significance level.

The final analyses will use a mixed effects model to incorporate correlations between the observations made by the same physician. The variance in 5A scores taken from patients within a single physician's patient panel will likely be smaller than the variance of scores taken from patients between different physicians, i.e. the intraclass correlation coefficient (the ratio of between-physician variance to the sum of between- and within-physician variances) will be larger than zero. We have conducted a series of power analyses taking this clustering into effect using a Mann–Whitney two-sample t-test of means.

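### The primary mixed model uses baseline 5A scores both as an outcome time point and as a covariate, which makes the standard error of the between-group difference after training about 10–15% too small

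*Protocol article*

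**What the plan says.** The Statistical analyses section says that the primary mixed model will "compare mean 5As scores between and within each group for each of the three time points: baseline, immediately post-intervention, and follow-up". Baseline is therefore one of the outcome levels. After Figure 2 the same section lists the model terms: "The clinicians will be included as a random effect, and intervention group, time, and baseline 5A scores will be included as fixed effects". It adds: "The interaction between treatment and time will be used to assess whether the treatment effect (of the intervention) changes with time". Nothing in the article removes the baseline visits from the outcome.

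The Sample size and power section gives the purpose of the random effect, which is to "incorporate correlations between the observations made by the same physician". It powers a difference of 0.54 between Groups 1 and 2. The Design limitations section says that no patient cohort is followed before and after training. The Data management section fixes the level: "all statistical tests will be performed at the two-tailed 5% level of significance".

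**The concern.** A post-training visit has no baseline score of its own, because that patient was not seen at baseline. The natural covariate is the mean of the clinician's baseline visits, and the model also treats those visits as outcomes. For the baseline rows the clinician mean is thus regressed on itself, with a slope of one. The pooled slope is pulled upward, and clinician differences that should feed the random effect are absorbed by the covariate.

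The random effect then cannot fully do the job that the sample size section gives it. The contrast at risk is the group difference at a given post-training time point, which the analysis section plans and the sample size section powers. With 15 randomised clinicians, an interval that is too narrow could present ordinary clinician-to-clinician variation as a training effect.

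**Working it through.** **Inputs.** From the protocol: two-sided 5%; "planned maximum of 15 clinicians (eight in Group 1 and seven in Group 2"; "approximately 10 recordings at baseline and seven or eight each at post- and follow-up points", which after the stated 20% loss is 8, 6 and 6 visits; SD 1.06. Assumed: the ICC (ρ), which the protocol says only exceeds zero, at 0.05, 0.10 and 0.20. Clinician-by-time variance, for which no value is given, is zero in steps 1–5. Variances are fractions of the total, so the SD cancels from the ratios.

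**The plan's own figure.** Treating 160 and 140 visits as independent, the detectable difference at 80% power is (1.96 + 0.84) × 1.06 × √(1/160 + 1/140) = 0.344, not 0.54. With 64 and 56 visits (eight per clinician, one time point) it is 0.543. The stated 0.54 thus fits a single time point, or 20 visits per clinician with an unstated ICC of about 0.078. This is a separate matter. It is relevant here only because it shows that a between-group difference is what was powered.

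**Step 1, baseline slope.** From post visits alone the slope is λ = 8ρ/(8ρ + 1 − ρ). With 8 of 20 visits at baseline contributing a slope of 1, the fitted slope is b = 0.4 + 0.6λ. At ρ = 0.10, λ = 0.8/1.7 = 0.47 and b = 0.68.

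**Step 2, clinician variance.** After adjustment, a clinician's 20-visit mean has variance 0.36 × [ρ(1 − λ) + (1 − ρ)/12]. The model subtracts (1 − ρ)/20 from this to estimate the clinician variance. At ρ = 0.10 that is 0.0461 − 0.0450 = 0.001, while the clinician variance left after conditioning on the baseline mean is ρ(1 − λ) = 0.053. At ρ = 0.05 the result is 0.0412 − 0.0475, which is negative and so set to zero. At ρ = 0.20 it is 0.0480 − 0.0400 = 0.008, against 0.067.

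**Step 3, standard error at immediate post.** The true variance per clinician is ρ(1 − b)² + (1 − ρ)/6 + b²(1 − ρ)/8. At ρ = 0.10 this is 0.0101 + 0.1500 + 0.0524 = 0.2125. The model counts about 0.001 + 0.150 = 0.151. The SE ratio is √(0.151/0.2125) = 0.84. The same sum gives 0.87 at ρ = 0.05 and 0.83 at ρ = 0.20. These figures ignore the error in the slope and the truncation of the variance at zero, so simulation should give slightly higher ratios.

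**Step 4, contrasts that escape.** The covariate has the same value in a clinician's baseline and post rows, so it cancels from any change over time. Group-by-time and within-group change should therefore keep their level.

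**Step 5, simulation under no effect** (REML, random clinician intercept, 8 vs 7 clinicians, 3000 runs per column):

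| | ICC 0.05 | 0.10 | 0.20 |
|---|---|---|---|
| Group difference at post, as written, residual df | 8.1% | 9.2% | 9.4% |
| Same, 12 df | 5.0% | 6.3% | 6.3% |
| Same contrast, no baseline covariate, residual df | 4.4% | 5.9% | 5.9% |
| Model SE / true SD, as written | 0.90 | 0.85 | 0.86 |
| Runs with clinician variance estimated as zero | 70% | 56% | 40% |
| Group-by-time, as written, residual df | 5.4% | 5.7% | 4.6% |
| Change within Group 1, as written, residual df | 5.4% | 5.1% | 5.4% |

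A repeat of the simulation gave 7.2–9.4% with residual df and 4.4–6.6% with 12 df. Another, with 13 df, gave 5.5–7.4% and SE ratios of 0.89–0.85.

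**Step 6, the secondary point.** If clinician-by-time variance is 2%, 5% or 10% of the total (assumed), the group-by-time test with a clinician intercept only rejects 6.3–6.4%, 8.3–10.4% and 12.4–14.5%. Without the baseline covariate the range over these cases is almost the same (6.1–14.5%), so this inflation comes from the random-effects structure and not from the double use.

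**The case against.** The strongest defence is that the primary hypothesis is a change from baseline and the only other test named is group-by-time, and the double use leaves both near 5%. That is correct. A reader might infer that every 5% test in this model is too liberal, or that all time contrasts have intervals that are too narrow. Steps 4 and 5 do not support that.

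Second, the 8–9% figures depend on residual degrees of freedom, and the article names no method. That also stands: with 12 df the excess is small. The standard error is too small under either choice.

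Third, the interaction wording fits a model of post-baseline visits adjusted for baseline, in which group carries the effect and the interaction asks whether it lasts. That would be a sound model. But the preceding paragraph has the same model compare means "for each of the three time points: baseline, immediately post-intervention, and follow-up", and no text drops the baseline rows, so the benign reading conflicts with the stated one.

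Fourth, the article says that clinicians are a random effect. It does not say intercept only, and a condensed article may leave further terms and degrees of freedom to a fuller plan. A reader might infer that rejection rates well above 10% are a demonstrated property of this trial. They are not: they need a clinician-by-time variance that the protocol does not give. This part therefore stays conditional.

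**Conclusion.** The point holds for one planned and powered comparison. As written, baseline stands on both sides of the primary model, and the standard error of the between-group difference at a post-training time point is about 10–15% too small. A nominal 5% test of it rejects about 7–9% under the null with residual degrees of freedom, and about 4–7% with 12. Group-by-time and within-group change are not affected by the double use alone.

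These sizes rest on an assumed ICC of 0.05–0.20, on the clinician's baseline mean as the covariate, on 8/6/6 analysable visits, on normal scores, and on three time points in both groups, although Group 2 may have four. The real score runs from 0 to 5 with a mean below its SD, and it is defined for visits in which activity is raised. The percentages are therefore indicative.

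The random-effects point is secondary. If 5–10% of the variance were clinician-by-time, the group-by-time test would reject about 8–14%. Some variation in response to training is plausible, but its amount is unknown here.

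**What to change.** Use baseline once and say how. There are two options:

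- Model only post-baseline visits, with the clinician's baseline mean as covariate. The group term is then the effect, and the interaction shows whether it lasts.
- Keep baseline visits as outcome rows and drop the covariate. The group-by-time term is then the baseline-adjusted effect.

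As a safeguard, add a clinician-by-period random effect with small-sample degrees of freedom such as Kenward–Roger, or analyse clinician-level means. In 12 simulated scenarios with clinician-by-time variance from 0 to 10%, the post-only model with 12 df, testing the group effect averaged over both post time points, rejected 2.5–5.5%. A t-test of clinician-level change scores with 13 df rejected 4.3–5.7%.

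The cost is a sentence of model specification and a few lines of SAS. No new data are needed. Intervals become somewhat wider.

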**Figure 1 F1:**
[figure not shown]
Study Schema.

The project is a two-arm randomized pragmatic trial to pilot a communication training intervention for primary care clinicians (n=13) on use of the 5As to promote physical activity in underserved patients. The intention of training focuses on clinicians to communicate effectively using the 5As and patient-centered communication skills firmly linked to a theory of human motivation (Aim 1). Clinicians are randomly assigned to two groups. Group 1 participates in the training intervention first; Group 2 receives the intervention six months later. The primary outcome is the frequency and quality of clinician use of the 5As during routine office visits, post-intervention compared to baseline. Secondary outcomes and potential mediators are changes in patients’ perceived competence to adopt physical activity (Aim 2) and clinician autonomy support of physical activity with their patients (Aim 3). Given the myriad of barriers reported in the literature, another secondary outcome is whether clinicians believe that the intervention addresses pertinent barriers to promoting exercise (Aim 4). Exploratory outcomes are other potential mediators of the intervention’s effect and the effect of the intervention on actual physical activity levels in a subset of participants. The schema shows the overall study design and timeline.

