### Group 2 (wait-list)

The clinician baseline assessment for Group 2 is identical to that for Group 1. The Group 2 assessment occurs at 0–3 months (concomitant with the Group 1 clinician baseline) and again at 9–12 months (concomitant with the Group 1 post-intervention assessment.)

Group 2’s clinician training intervention occurs in the same manner as described in the section, Description of Intervention (section 2.11) for Group 1. Standardization of both Group 1 and Group 2’s training intervention sessions is assessed by audio-recording all sessions and ensuring that the key objectives of each session are met using a pre-developed checklist and via rating by a trained research staff member not involved in delivering the intervention.

Group 2’s Post-Intervention Assessment occurs immediately post-intervention and at six months post-intervention in the same manner as described previously for Group 1 (section Post-Intervention Clinician Assessment). As with Group 1, Group 2 clinicians also complete a survey asking about the feasibility of the intervention and individual exit interviews.

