### Evaluation and measures

#### Primary outcome measure: 5As score

The primary outcome measure is the 5As score, a score of the frequency and quality of 5As discussions about physical activity. Based on our previous pilot study and others’ published work [11,15,53,54] we developed a coding form to capture the 5As from audio-recorded office visit discussions. The 5As score has two components: 1) the sum of each A of the 5As occurring in each office visit when the topic of physical activity is raised (range 0/no As used to 5/all As used) and 2) a rating of the quality of each A when it occurs (ranging from 1–3 based level of detail from minimal to intensive). The 5As score is measured at baseline, immediately post-intervention, and at six months follow-up for Groups 1 and 2. The 5As score is assessed by trained research staff blinded to clinician and time point.

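### The group-by-time interaction is named as the test of whether the training effect changes with time, but because both groups are trained it tests only whether their courses differ

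*Protocol article*

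**What the plan says.** All places are in the protocol article.

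- **Statistical analyses, named test.** "The interaction between treatment and time will be used to assess whether the treatment effect (of the intervention) changes with time".
- **Statistical analyses, model.** Clinician is a random effect, and "intervention group, time, and baseline 5A scores will be included as fixed effects". The stated purpose is to "compare mean 5As scores between and within each group for each of the three time points: baseline, immediately post-intervention, and follow-up", so baseline is listed as a time level and baseline score is also a covariate.
- **Study design.** "Group 1 participates in the training intervention first; Group 2 receives the intervention six months later". Group 2 is a wait-list group, not a control that stays untrained.
- **Primary outcome measure.** "The 5As score is measured at baseline, immediately post-intervention, and at six months follow-up for Groups 1 and 2".
- **Group 2 (wait-list).** Its post-intervention assessment "occurs immediately post-intervention and at six months post-intervention in the same manner as described previously for Group 1". Before its training it is assessed at 0–3 months and "again at 9–12 months (concomitant with the Group 1 post-intervention assessment").
- **Sample size and power.** Clinicians are "measured at three (Group 1) or four (Group 2) time points". The article does not say how Group 2's four points map onto the three in the model.

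**The concern.** The sentence sets a question (does the effect of training change with time?) and a test for it. In a trial with one trained and one untrained arm, and time limited to points after training, a group-by-time term would answer that question, because the group difference at each time is the training effect. Here both groups are trained and their time points are set by their own training. The group difference at the post and follow-up points is then a difference between two trained groups, not a training effect, and its change over time says nothing about whether the gain lasts.

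Persistence matters to this trial. H1 and H2 refer to the period immediately after training and at one year, and the limitations section warns that improvement may be hard to sustain. If the sentence is followed, a non-significant interaction invites the statement that the effect did not change with time, even when the whole gain has gone in both groups.

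**Working it through.** **Inputs from the article.** 8 and 7 clinicians; about 20 analysable visits per clinician; SD 1.06; pilot mean 0.74; difference 0.54; two-sided 5%.

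**Assumptions.** ICC 0.07 (checks at 0.05 and 0.10 gave similar results; the article gives no ICC). Visits split 8/6/6 over baseline, post and follow-up in both groups, although Group 2 has four points.

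**The article's own figure.** With 160 v 140 visits and a plain t-test, the difference detectable at 80% power is (1.96 + 0.84) × 1.06 × √(1/160 + 1/140) = 0.344, not 0.54. The figure 0.54 is recovered with 8 visits per clinician (64 v 56: 0.543) or with an unstated ICC of about 0.077 (0.539). It is used here only as a scale for the gain; the point does not depend on it.

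**Step 1, algebra on own-training time.** Write m(g,t) for the mean score of group g at time t. The interaction contrasts are

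- [m(1,post) − m(1,base)] − [m(2,post) − m(2,base)]
- [m(1,follow-up) − m(1,base)] − [m(2,follow-up) − m(2,base)]

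Both groups gain 0.54 and lose it all: 0.54 − 0.54 = 0 and 0 − 0 = 0. Both groups gain 0.54 and keep it: 0 and 0 again. The term cannot separate these two cases at any sample size or ICC.

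**Step 2, simulated rejection rates at 5%.** Every clinician within a group changes alike.

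| Scenario | Interaction, three time levels | Follow-up minus post, pooled |
|---|---|---|
| Own-training time, 0.54 kept in both groups | about 5% | about 5% |
| Own-training time, 0.54 fully lost in both | about 5% | 94% |
| Own-training time, half lost in both | about 5% | about 43% |
| Own-training time, lasting gains of 1.08 and 0.54 | about 50% | about 5% |
| Calendar time, Group 2 trained by Group 1's follow-up, lasting 0.54 | about 45% | not applicable |
| Calendar time, same, 0.54 fully lost | about 89–91% | not applicable |

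In the fifth row the group differences are 0, 0.54 and 0: the gap closes because Group 2 has been trained, not because the effect has faded. On calendar time the interaction rejects for both a lasting and a lost effect, so a rejection does not identify fading.

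**Step 3, baseline as covariate only.** With time limited to post and follow-up, lasting unequal gains are no longer flagged (about 5%). A common fade remains invisible (about 5%), and calendar coding still flags a lasting 0.54 effect in about 42–43%.

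**Step 4, power of the direct contrast.**

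- Pooled over visits, 90 v 90: SE = 1.06 × √0.93 × √(2/90) = 0.152; 0.54/0.152 = 3.54; power about 94%.
- Clinician-level paired differences: within-clinician variance 1.06² × 0.93 = 1.045; variance of one clinician's difference 2 × 1.045/6 = 0.348; SE = √(0.348/15) = 0.152; power about 90% on 14 df.
- With an assumed clinician-by-time SD of 0.3: variance 0.348 + 2 × 0.09 = 0.528; SE = √(0.528/15) = 0.188; 0.54/0.188 = 2.88; power about 75%. For half loss it is about 28%. At an SD of 0.5, power for full loss is about 57%.
- With that SD of 0.3, a model with only a random clinician intercept rejects a truly sustained gain in about 10–12% of trials, so the error term needs care.

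**The case against.** The strongest reply is that fading would not go unexamined. The statistical section plans comparisons within each group across the three time points, and the data management section plans 95% confidence intervals for differences in mean score across time points. H1 compares the later period with baseline, so a gain wholly lost by one year should appear as no difference there. This stands. A reader might infer that the trial cannot detect a lost gain, or that the H1 test is at fault; the article supports neither. It does not rescue the sentence, which gives this question to the interaction, while the hypotheses specify change from baseline and never follow-up against immediately post.

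A second reply is that the interaction is not always blind. If only one group fades, it can react. This also stands, but the reaction does not show that the training effect as a whole fades.

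A reader might also infer that the interaction routinely flags a lasting effect as changing. With time counted from own training and equal gains it keeps its 5% level; false flags need calendar coding, or unequal gains with baseline as a time level. Nor should one picture Group 2 as untrained at all three time levels: the article gives it only two assessments before training.

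Finally, time coding is commonly left to a full analysis plan, and whether baseline is a time level or only a covariate is unsettled here. But the point is a stated rule, not a missing detail, and under neither coding does the term test durability.

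**Conclusion.** The point holds in a limited form. On the article's own definition of the time points, the group-by-time interaction tests whether two trained groups run in parallel. A fade common to both leaves it at its nominal 5%, even if the whole 0.54 is lost; this is exact and needs no assumption about variance. The false-flag rates are conditional: about 45% for a lasting 0.54 under calendar coding with Group 2 trained by Group 1's follow-up, and about 50% for lasting gains that differ by 0.54 when baseline is a time level. These rates rest on the assumed ICC, the 8/6/6 split and no clinician-by-time variation.

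The consequence is confined to how durability is judged and reported. It is worth correcting before analysis because the remedy is small.

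**What to change.** Replace the sentence with: *Whether the training effect changes with time will be assessed by the contrast follow-up minus immediately post-intervention (time counted from each group's own training), within clinician and pooled over both groups, with its 95% CI, from a model that allows clinician-by-time variation or from clinician-level paired differences. A non-significant result alone will not be read as a sustained effect.* Keep the group-by-time term only to ask whether the two groups' courses differ.

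The cost is one contrast and one reworded sentence, with no new data. There are two limits. The contrast is not a randomized comparison, and it controls calendar trend only partly, through the groups reaching follow-up at different dates. With 15 clinicians, a partial fade may well be missed, which is why the confidence interval should be reported.
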